### Sample size calculation

The sample size calculation is based on previous studies [14, 20, 21]. The routine basic treatment has been proved to improve the MOCA score of patients with CSVD by 2 points [20]. Besides, the routine basic treatment combined with Yinxingye is effective in the treatment of cognitive impairment in non-demented patients, with a MOCA score improved by 3 points [21]. Moreover, Wu et al. have found that Dengyinnaotong Capsule is better than Yinxingye Capsule in terms of effective rate and improvement symptoms in the treatment of ischemic stroke [14]. Therefore, based on the above results, we assume that the routine basic treatment combined with Dengyinnaotong Capsule in this trial will improve the MOCA score of patients with CSVD by 2 points compared with the routine basic treatment. Accordingly, 108 per group will be sufficient with a level of significance of 95% (*α*=0.05), a power of 90% (*β*=0.1), and an assumed standard deviation (SD) of 4.5. Considering the drop-out rate of 20%, a total of 270 samples (135 per group) are needed at least.

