### Data collection

In this trial, data collection will be performed at weeks 0, 4, and 12 in the treatment period. The schedule of data collection is shown in Table 1. General biochemical examinations include blood routine, urine routine, stool routine, coagulation function, liver function, renal function, blood glucose, and blood lipid examination.

**Table 1 Tab1:** Schedule of data collection

Visits	Screening and baseline	Treatment period	
	0	1	2
Time points (weeks)	− 1 to 0	4	12
Time windows (days)	-	±7	±7
Informed consent	×		
Inclusion and exclusion criteria	×		
History of diagnosis and treatment	×		
Vital signs and physical examinations	×	×	×
General biochemical examinations	×	×	×
12-lead electrocardiogram examination	×	×^a^	×
CT or MRI examination	×	×^a^	×^a^
MoCA score	×		×
CDR score	×		×
Shape Trail Test	×	×^a^	×
ADL score	×		×
DHI score	×^a^	×^a^	×^a^
Tinetti POMA score	×^a^	×^a^	×^a^
GDS score	×^a^	×^a^	×^a^
Serum levels of Hcy, HS-CRP, and D-dimer	×	×	×
Audiological examination	×^a^	×^a^	×^a^
Drug combination	×	×	×

*MoCA* Montreal Cognitive Assessment, *CDR* Clinical Dementia Rating, *CT* Computed tomography, *MRI* Magnetic resonance imaging, *ADL* Activities Of Daily Living, *DH* Dizziness Handicap Inventory, *Tinetti POMA* Tinetti performance-oriented mobility assessment, *GDS* Geriatric Depression Scale, *Hcy* homocysteine, *HS-CRP* High-sensitivity C-reactive protein

^a^For patients with relevant clinical manifestations or willing to be examined

The 30-item clinician-administered MoCA is a brief cognitive screening tool with high sensitivity for screening patients with mild cognitive impairment [22]. It is a simple 10-min paper-and-pencil test that assesses multiple cognitive domains including memory, attention, concentration, language, visuospatial skills, abstraction, calculation, executive functions, and orientation.

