### Outcomes

The primary outcome is the change in MoCA score from baseline to week 12. The secondary outcomes include the following: (1) the changes in STT, ADL, GDS, and DHI score from baseline to week 12; (2) new vascular events; and (3) the changes in serum level of homocysteine (Hcy), high-sensitivity C-reactive protein (HS-CRP), and D-dimer from baseline to week 4 and 12, respectively. The exploratory outcome is the changes in the Tinetti POMA score from baseline to week 12.

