### Statistical analysis

The efficacy analysis is based on the intention-to-treat (ITT) population, which is defined as all randomized participants. All efficacy analysis results are analyzed in the full analysis set (FAS) and per-protocol set (PPS). The FAS is defined as all randomized patients who received at least one dose of the study drug and had both baseline and at least one post-baseline measurement of primary efficacy. The PPS is defined as all patients who completed the treatment without serious violation of the protocol. The safety analysis is performed in a safety set (SS), which is defined as participants who receive at least one dose of the study drug and at least one assessment of safety data. Categorical data will be expressed as numbers and percentages, and quantitative data will be expressed as means±SD, median, interquartile range (IQR) values, or minimum and maximum. For the primary outcome, the analysis of covariance (ANCOVA) will be performed to compare the 12-month MoCA outcomes (the change in MoCA score from baseline to week 12) between the groups at follow-up adjusting for baseline scores. For secondary and exploratory outcomes, the ANCOVA will also be performed to test for statistical differences between the groups. A repeated-measures analysis of variance (ANOVA) was performed to investigate the time-course of the changes in serum level of Hcy, HS-CRP, and D-dimer from baseline to weeks 4 and 12 within each group and to compare those between two groups. Pearson *χ*^2^ or Fisher’s exact test will be performed to compare differences in AEs of two groups. Any potential effects related to site differences will be assessed using mixed models. The baseline will be taken as the covariate in the model, and the effect of the center will be considered. In the case of missing data, we will capitalize on multiple imputation techniques to handle the issue of missing data in this study. All statistical analyses will be performed using Statistical Analysis System (SAS Institute, Inc, Gary, NC), and statistical significance was set at *p*<0.05.

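### Homocysteine, HS-CRP and D-dimer each get two between-group analyses with no order of precedence, and the repeated-measures ANOVA as worded is not baseline-adjusted

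*Protocol article*

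**What the plan says.** The Outcomes section lists among the secondary outcomes "the changes in serum level of homocysteine (Hcy), high-sensitivity C-reactive protein (HS-CRP), and D-dimer from baseline to week 4 and 12, respectively". The schedule in Table 1 (Data collection) has the row "Serum levels of Hcy, HS-CRP, and D-dimer" marked at baseline, week 4 and week 12.

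The Statistical analysis section then makes four statements that bear on these markers:

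- A general rule: "For secondary and exploratory outcomes, the ANCOVA will also be performed to test for statistical differences between the groups".
- A specific rule in the next sentence: "A repeated-measures analysis of variance (ANOVA) was performed to investigate the time-course of the changes in serum level of Hcy, HS-CRP, and D-dimer", continuing "from baseline to weeks 4 and 12 within each group and to compare those between two groups".
- After a sentence on site differences and mixed models: "The baseline will be taken as the covariate in the model, and the effect of the center will be considered".
- One threshold for everything: "statistical significance was set at *p*<0.05".

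**The concern.** The three markers fall under both the general and the specific rule. Both rules promise a comparison of the arms, and no sentence ranks them or calls one supportive. If the two disagree, the plan does not say which is the result.

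The second method is also the weaker one as described. The only sentence that makes baseline a covariate in a model with centre follows the mixed-model sentence and is not tied to the repeated-measures ANOVA. That leaves two readings. Baseline may be one of three levels of time, in which case the group effect averages in a visit before any treatment. Or the ANOVA may be run on unadjusted change scores at weeks 4 and 12. Neither uses baseline as well as a covariate does.

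Finally, the plan examines change within each arm. Such change mixes any drug effect with background care and regression to the mean. The Sample size calculation section itself expects MoCA to rise by 2 points on routine treatment alone, so change without the study drug is already part of the planning.

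At stake is how three secondary outcomes will be read: more chances of a positive result than the stated 5%, and a less precise estimate if the ANOVA is the one reported.

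**Working it through.** **The plan's own figure.** The article gives no sample size or power for the markers. Its only calculation is for MoCA: difference 2, "a power of 90% (*β*=0.1), and an assumed standard deviation (SD) of 4.5", with α = 0.05 taken as two-sided. n = 2 × [4.5 × (1.960 + 1.282) / 2]² = 106.4, so 107 per group against 108 stated; power at 108 is 0.904. Then 108 / 0.80 = 135 per group, 270 in all. This reproduces and is not in dispute.

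**Assumptions for the markers.** The article gives no marker distributions, effects or correlations. I take unit SD at each visit, equal correlation ρ between visits (0.3, 0.5, 0.7), the same effect δ at weeks 4 and 12, and 108 per group.

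**Step 1: baseline as a level of time.** The group effect is (0 + δ + δ)/3 = 2δ/3. The mean of three visits has variance (1 + 2ρ)/3. To compare with an unbiased estimate of δ, divide by (2/3)² = 4/9. Week-12 ANCOVA has variance 1 − ρ².

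| ρ | Group effect, rescaled | Week-12 ANCOVA | Ratio |
|---|---|---|---|
| 0.3 | 0.533/0.444 = 1.20 | 0.91 | 1.32 |
| 0.5 | 0.667/0.444 = 1.50 | 0.75 | 2.00 |
| 0.7 | 0.800/0.444 = 1.80 | 0.51 | 3.53 |

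Against a baseline-adjusted mean of weeks 4 and 12, variance (1 + ρ)/2 − ρ², the ratios are 2.14, 3.00 and 5.00.

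**Step 2: unadjusted change scores.** Change at one visit has variance 2(1 − ρ).

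- ρ = 0.3: 1.40/0.91 = 1.54
- ρ = 0.5: 1.00/0.75 = 1.33
- ρ = 0.7: 0.60/0.51 = 1.18

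These compare one visit with the same visit. For the mean over both visits, change has variance (1 + ρ)/2 + 1 − 2ρ, and the like-for-like ratios are 1.05/0.56 = 1.88, 0.75/0.50 = 1.50 and 0.45/0.36 = 1.25.

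**Step 3: power at δ = 0.4 SD, baseline as a level.** The group-by-time test has noncentrality (108/2) × Σ(e − ē)²/(1 − ρ) with e = (0, 0.4, 0.4). That is 54 × 0.1067/(1 − ρ) = 5.76/(1 − ρ), on 2 and 428 degrees of freedom.

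| ρ | Week-12 ANCOVA | Group effect | Group-by-time | Baseline-adjusted mean of weeks 4 and 12 |
|---|---|---|---|---|
| 0.3 | 0.87 | 0.77 | 0.73 | 0.98 |
| 0.5 | 0.92 | 0.67 | 0.87 | 0.99 |
| 0.7 | 0.98 | 0.59 | 0.98 | 1.00 |

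**Step 4: several tests, no precedence.** In 4,000 simulated trials per correlation with no true effect, at least one of week-12 ANCOVA, group effect and group-by-time had p < 0.05 in 11.8%, 11.9% and 12.9%. Simulations with log-normal values at correlation 0.6 gave about 10 to 12%. The repeated-measures ANOVA alone accounts for most of this: its two terms are independent under the assumed correlation structure, so 1 − 0.95² = 9.75%. A separate week-4 ANCOVA was not counted; it could only raise the figure.

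**Step 5: disagreement.** With a true effect of 0.4 SD, ANCOVA and group-by-time differed on significance in 26%, 13% and 2% of trials (ρ = 0.3, 0.5, 0.7).

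**The case against.** The strongest defence is a division of labour: ANCOVA for the contrast, repeated-measures ANOVA to describe the trajectory. The opening of the ANOVA sentence supports that. Its ending does not, because it extends the ANOVA to a comparison of the two groups, so the overlap remains.

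A second defence is that the group effect is the wrong term for a difference in time-course; group-by-time is the right one. That is fair, and it lowers the figure in Step 4. With ANCOVA and group-by-time only, the null rates were 4.8% and 5.2% with 6.05% disagreement at ρ = 0.3. Both were therefore significant in (10.05 − 6.05)/2 = 2.0%, and at least one in about 8%. The same arithmetic gives about 8% at the other correlations. The excess shrinks but does not vanish, and the plan does not name the term.

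A reader might infer more than the text supports:

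- **That both analyses are inefficient.** ANCOVA is the efficient one, and group-by-time loses almost nothing at ρ = 0.7.
- **That the two contradict each other.** They are duplicated and unreconciled; one could be supportive if the plan said so.
- **That baseline is certainly a time level.** The wording and the schedule suggest it, but change scores also fit.
- **That patients missing a visit are dropped.** The same section plans multiple imputation.
- **That skewed values on the raw scale cost much power.** The article gives no marker distributions, and a transformation is commonly left to the SAP, which is not shown.
- **That efficacy will be claimed from within-arm p-values.** A between-group comparison is explicitly planned; the problem is only that within-arm tests stand beside it without a stated role.

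**Conclusion.** The point holds for the duplication, for the lack of stated baseline adjustment in the repeated-measures ANOVA, and for the undefined role of within-arm tests. The first rests on the text alone.

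The sizes rest on assumptions. The dilution to two thirds needs baseline as a time level and an equal effect at both visits. The 1.2 to 1.5 variance ratio applies to change scores at a single visit with correlation 0.3 to 0.7. The 10 to 13% needs baseline as a time level and any significant term being accepted as the result. It does not apply if one test is named beforehand.

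The consequence is limited. Three secondary outcomes are affected, in a trial that its Study design section calls exploratory. The primary MoCA ANCOVA and the 108, 135 and 270 are unchanged. It is worth correcting because the plan states the weaker method explicitly and a better one costs almost nothing.

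**What to change.** For these three markers, replace both the repeated-measures ANOVA and the separate ANCOVA with one longitudinal model per marker. The outcome is the week-4 and week-12 values; the terms are baseline, treatment, visit and treatment-by-visit, with correlation between the two visits allowed for. Centre can be handled as the plan already intends. Report the between-group contrasts at weeks 4 and 12 with 95% confidence intervals, and present within-arm change descriptively, without tests.

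Optionally, use the log scale if the distribution pooled over both arms, examined without treatment codes, is skewed. The contrasts then read as ratios of geometric means.

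The cost is a change of wording before database lock. It needs no new data, no extra visits and no software beyond the SAS already named.

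### Homocysteine, HS-CRP and D-dimer get two between-group analyses with neither named as decisive, plus within-arm significance tests that are not randomized comparisons

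*Protocol article*

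**What the plan says.** The Outcomes section lists the changes in homocysteine (Hcy), "high-sensitivity C-reactive protein (HS-CRP), and D-dimer from baseline to week 4 and 12, respectively", among the secondary outcomes. The schedule in Table 1 has these markers measured at screening/baseline, week 4 and week 12.

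The Statistical analysis section then contains two rules that both apply to them:

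- The general rule: "For secondary and exploratory outcomes, the ANCOVA will also be performed to test for statistical differences between the groups".
- The marker-specific rule: "A repeated-measures analysis of variance (ANOVA) was performed to investigate the time-course of the changes in serum level of Hcy, HS-CRP, and D-dimer", taken "from baseline to weeks 4 and 12 within each group and to compare those between two groups".

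A later sentence, placed after the one on mixed models for site differences, adds: "The baseline will be taken as the covariate in the model, and the effect of the center will be considered". It does not say which model is meant. One threshold covers everything: "statistical significance was set at *p*<0.05".

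**The concern.** Two features of this text cause trouble.

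First, both rules compare the arms on the same three outcomes, and neither is given precedence. The ANOVA sentence also does not say whether its between-group test is the group main effect or the group-by-time term. These tests answer different questions and can disagree, so the reported result could be chosen after the data are seen.

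Second, the ANOVA is explicitly to be run inside each arm. A change over time within one arm mixes any effect of the capsule with everything else that moves a marker over 12 weeks, such as routine treatment, regression to the mean and assay drift. Randomization protects only the contrast between arms. A significant change on the capsule and none on control is easily read as an effect, although it can arise often when the arms do not differ. The trial is open-label, so the temptation to read it that way is real.

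What is at stake is the interpretation of three secondary biomarkers.

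**Working it through.** **Inputs.** The article gives no figure for the marker analyses, so there is none to reproduce. From the Sample size calculation section I take 108 evaluable patients per arm. That figure checks for MoCA: a 2-point difference, SD 4.5, α 0.05 and 90% power need 106.4, so 107 per arm, and 108 gives 90.4% power; 108/0.8 = 135 per arm, 270 in total. From Table 1 I take three measurement times. Assumed: unit SD, equal correlation ρ between visits of 0.5 or 0.7, a shared drift d at both post-baseline visits of 0 to 0.30 SD, and two-sided tests at 0.05.

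**Step 1: within-arm tests when the arms do not differ.** The arms are independent and each test has the same power p, so

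P(significant in the capsule arm only) = p(1−p).

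At p = 0.05 this is 0.05 × 0.95 = 4.8%; at p = 0.2 or 0.8 it is 16%; at p = 0.5 it reaches its maximum of 25% (50% for exactly one arm, whichever it is).

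**Step 2: p for a within-arm ANOVA over three times.** This step takes baseline as one of the time levels. With means 0, d, d, the sum of squared deviations from their mean is 2d²/3 and the within-patient error variance is 1−ρ. The noncentrality is therefore λ = 108 × (2d²/3)/(1−ρ), on 2 and 214 degrees of freedom. For d = 0.20 and ρ = 0.5, λ = 108 × 0.02667/0.5 = 5.76, p = 0.559, and p(1−p) = 0.246. The last column is from 3,000 simulated trials per row.

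| ρ | Shared drift (SD) | λ | p | p(1−p) | Simulated capsule-only |
|---|---|---|---|---|---|
| 0.5 | 0 | 0 | 0.050 | 4.8% | 5.3% |
| 0.5 | 0.10 | 1.44 | 0.171 | 14.2% | 13.9% |
| 0.5 | 0.15 | 3.24 | 0.340 | 22.4% | 22.9% |
| 0.5 | 0.20 | 5.76 | 0.559 | 24.6% | 23.6% |
| 0.5 | 0.30 | 12.96 | 0.903 | 8.8% | 8.3% |
| 0.7 | 0 | 0 | 0.050 | 4.8% | 5.1% |
| 0.7 | 0.10 | 2.40 | 0.261 | 19.3% | 18.7% |
| 0.7 | 0.15 | 5.40 | 0.531 | 24.9% | 25.6% |
| 0.7 | 0.20 | 9.60 | 0.793 | 16.4% | 15.6% |
| 0.7 | 0.30 | 21.60 | 0.990 | 1.0% | 0.9% |

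For drifts of 0.10–0.20 SD, 13–23% of simulated trials had a capsule-only result while the week-12 ANCOVA was not significant. The ANCOVA itself kept its error rate at 4.7–5.4% throughout.

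**Step 3: do the rival between-group tests differ?** With an assumed true effect of 0.30 SD at both post-baseline visits and baseline as a time level, simulated power was:

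| Test | ρ = 0.5 | ρ = 0.7 |
|---|---|---|
| Week-12 ANCOVA | 71% | 86% |
| Group-by-time term | 62% | 84% |
| Group main effect | 44% | 37% |

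**Step 4: the size of the estimate, conditionally.** If baseline is a time level and the group main effect is the test, the expected estimate is (0 + Δ + Δ)/3 = 2Δ/3, because randomization makes the expected baseline difference zero. Simulation agrees: 0.30 SD became 0.20, and 0.444 SD became 0.29–0.30, while the week-12 ANCOVA returned 0.30 and 0.44. The group-by-time term does not average baseline into the effect, and an ANOVA on change scores at weeks 4 and 12 would not shrink it.

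**The case against.** The best defence has four parts.

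- *Precedence and the choice of ANOVA term are detail for the analysis plan.* This is partly right: a condensed article may leave out which term is tested. But the article does more than stay silent. It states two between-group methods for the same outcomes, and it states the within-group tests.
- *The plan does not say that baseline is a time level.* This stands. A reader might infer from the reference to a time-course that the ANOVA uses weeks 0, 4 and 12 and so cuts the treatment effect by a third. The text does not support that as a fact. The outcomes are defined as changes from baseline, so change scores at weeks 4 and 12 are also a possible reading. Comparing time-courses points to the group-by-time term rather than the main effect. The sentence making baseline a covariate settles neither question. The shrinkage is therefore conditional on two unstated choices.
- *The drift is assumed.* This also stands. A reader might cite the Sample size calculation section as expecting change under routine treatment, but that passage concerns MoCA and says nothing of the three markers. The capsule-only rate depends strongly on drift, and a single figure near 25% would show only the worst case.
- *Nothing says that a within-arm p-value will count as evidence of efficacy.* That is true, and the harm is a risk rather than a certainty. But the plan schedules these tests without calling them descriptive.

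**Conclusion.** The point holds in a limited form. Two things are explicit: two between-group analyses for each marker without an order of precedence, and significance tests within each arm. With no difference between arms, the within-arm tests give a capsule-only result in about 5% of trials without drift, 14–26% at a shared drift of 0.10–0.20 SD, and 1–8% at 0.30 SD. These rates assume 108 per arm, correlations of 0.5–0.7, and baseline as a time level in the within-arm ANOVA; the 25% ceiling on the true probability needs only equal power in two independent arms (the simulated 26% reflects sampling error).

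The fall of the estimate to two thirds is a possible consequence, not an established one.

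The matter is confined to secondary biomarkers in a trial that the Study design section calls exploratory. It does not touch the MoCA primary analysis or the sample size. It lies between a minor point and one that should be corrected.

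**What to change.** Name one baseline-adjusted between-group analysis for each marker. Either of these would serve:

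- the ANCOVA already planned, applied at each visit; or
- a mixed model with the week-4 and week-12 values as responses and baseline as covariate.

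Report the week-12 difference as the result and the week-4 difference as supportive, each with a 95% confidence interval. Drop the repeated-measures ANOVA as a between-group test. Present within-arm changes descriptively, without p-values.

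This takes about two sentences in the Statistical analysis section and needs no new data. It can be done before the database is locked. The only loss is the within-arm p-values.

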### Register, ethics, and data management

This study has been prospectively registered on 25 April 2021 at the Chinese Clinical Trial Registry (ChiCTR2100045831). This trial is conducted by the Declaration of Helsinki and Good Clinical Practice Guidelines and approved by the ethics committee institutional review board of each participating center. Any change to the protocol will be approved by the relevant regulatory authorities and require participants to re-consent before continuing in the study. Data were collected on paper first, and then is being entered and managed by a designated Data Manager using EpiData software (EpiData 3.01 for Windows; The EpiData Association, Odense, Denmark). To ensure the accuracy of the data, two data managers will independently carry out data entry and proofreading. The regular oversight will be conducted by an experienced Clinical Research Associate by monitoring the quality, safety, and progress of the study. The database will be locked post reconciliation of all data. The locked database will be provided to the statisticians to conduct the independent statistical analysis. There are no interim analyses planned. Study findings will be disseminated through peer-reviewed publications and presentations at scientific meetings.

